# The effect of a tailored message package for reducing antibiotic use among respiratory tract infection patients in rural Anhui, China: a cluster randomized controlled trial protocol

**DOI:** 10.1186/s13063-023-07664-8

**Published:** 2023-10-04

**Keywords:** Antibiotics, Messages, Patient education, China, RCT

## Abstract

**Background:**

Antibiotics are over-used for patients with respiratory tract infections (RTIs) in primary care, especially in the rural areas of China.

**Methods:**

A cluster randomized controlled trial (RCT) will be carried out to estimate the effectiveness of a tailored message package for educating patients to reduce antibiotic use for symptomatic respiratory tract infections (RTIs). In the intervention group, patients will receive 12 short messages in 12 consecutive days. The whole process of the message design, modification, translation (of substitution variables), and sending will be facilitated by a user-friendly mini-computer program. The primary measure for assessment is the reduction in number of days in which antibiotics are used by patients with symptomatic RTIs. The secondary measures include (1) patients’ knowledge about and attitude toward antibiotics; (2) patients’ quality of life (EQ-5D-5L) and symptom severity and duration; (3) times of re-visits to clinics and antibiotics re-prescription for the same RTI episode; and (4) times of re-occurrence of RTIs and related health service seeking and antibiotics consumption.

**Discussion:**

This study will determine the efficacy of a 12-message intervention to educate patients to reduce excessive antibiotic use in rural China.

**Trial registration:**

ISRCTN29801086. Registered on 23 September 2022.

**Supplementary Information:**

The online version contains supplementary material available at 10.1186/s13063-023-07664-8.

## Background

Antibiotic resistance (ABR) has become an urgent public health problem worldwide [1]. China is among the largest countries of antibiotics consumption and excessive use in primary care is most prominent. The proportion of antibiotic use in patients with symptomatic RTIs is estimated to be over 80% [2–9]. Globally, about 700,000 people died of antibiotic resistance in 2014 and this figure will reach 10 million per year by 2050. If effective prevention and control measures are not taken, drug-resistant infections will cause economic losses of about 100 trillion US dollars [10].

A variety of measures have been taken in China to improve antibiotic use [11–15]. These include the introduction of antimicrobial drug monitoring networks, practice guidelines, prescription formularies, restrictions on antibiotic prescription authority for doctors at different levels, education of doctors and patients, and others. Most of these approaches have showed some effects [16]. However, contemporary efforts have been focused primarily on doctors, with far less attention being put on patients [17, 18]. Antibiotic prescription reflects the joint interaction between the doctor and patient. Although the doctor dominates most of the consultation encounters, the patient also has important direct and/or indirect influences on the prescription decisions. Doctors often attribute excessive antibiotic use to “patient pressure and expectations” or “patient demand” [19]. They feel that their patients may be more satisfied if they were prescribed some medicine even if it is unnecessary. However, over 70% of patients reported that they would comply with their physician’s decision of not giving any prescription [20].

According to our previous studies and others, patients in China have various beliefs and habits that lead to excessive use antibiotics. They lack a general understanding of uses, especially resistance and other side effects, of antibiotics [21]. Some of them believe that antibiotics help in treating almost all diseases. Although China policy requests that (since 2020) all antimicrobials must be dispensed with a prescription in all retail pharmacies [22, 23], it is not fully enacted in rural areas [24, 25]. As a result, patients can easily get antibiotics from retail pharmacies without prescriptions. In addition, most consultations in China are very short and doctors seldom have time or desire to discuss antibiotics with their patients, while patients on the other hand seldom have the opportunity to explicitly express their expectations about antibiotics. These all point to a clear need for patient education. This study is an innovative attempt in this regard.

## Methods/design

The trial protocol was designed according to the SPIRIT reporting guidelines [26].

### Aim and objectives

#### Aim

This study aims to establish and validate a tailored message package (TMP) for reducing antibiotic use among patients clinically diagnosed with RTIs.

#### Objectives

To determine the effectiveness of the TMP in terms of reduced duration of antibiotic usage among patients with RTIs compared with those in the usual care (UC) arm.To compare knowledge and attitudes about antibiotics and use or reuse of health care for this and recurrent RTI episodes among patients between the TMP and UC groups.To assess the difference in quality of life between the TMP and the usual care arm

### Study settings

The RCT will be implemented in Anhui, an inland province in China. The study sites are township or community health centers in the province which are selected through the following steps: (1) select 2 cities from the province using convenience sampling; (2) randomly select 3 counties from each of the cites selected; (3) randomly select 4 nonadjacent township or community health centers from each of the selected counties (Fig. 1); and (4) randomly select equal number of township or community health centers from the none selected centers within the same county to substitute those that were selected via previous step yet declined to participate.

**Fig. 1 Fig1:**
[figure not shown]
Trial flow chart

### Trial design

The study adopts a cluster randomized controlled trial (RCT) design, involving two arms of equal townships or community health centers, i.e., the TMP arm or the UC arm.

### Allocation to study arms

The recruited township or community health centers will be randomly allocated to TMP and UC arms at the same time after the completion of baseline data collection. The allocation process will be performed by an external statistician via 4 steps. Step 1, the project facilitator sends, via email, the allocation requirements alongside the name-list of the 6 selected counties and the 4 health centers recruited under each of the counties to the external statistician. Step 2, the statistician performs the random assignment of the health centers into equal arms of TMP and UC using the “random sample of cases” function in IBM SPSS on a county-by-county base so that the 4 health centers recruited from each of the site counties is randomly assigned as 2 to the TMP arm and the other 2 to the UC arm. Step 3, the statistician emails back the resultant allocation to the project facilitator. Step 4, the facilitator communicates the allocation to the participating physicians and arranges the planned training for those in the TMP arm.

### Blinding

Given the nature of the intervention, doctors, telephone interviewers, and site investigators will not be blinded to the assigned condition since TMP is mentioned during the patient-doctor encounters and in the interviews. However, the statisticians responsible for the analysis will be blinded to the allocation until the quantitative analysis has fully completed. Unblinding is not relevant to this trial.

### Interventions

#### Usual care

The intervention will be tested against usual care. In other words, the control group will maintain usual care, while the intervention group patients will receive, in addition to usual care, 12 short messages in 12 consecutive days after the consultation. Here, usual care refers to the existing procedures (mainly, history inquiries, physical checkup, lab tests, clinical diagnosis, and prescribing treatment) being routinely practiced in the consultation and management of patients with RTIs. Using UC as the control condition is advantageous in at least a couple of senses: it involves almost no further changes in the control group and is thus most easy to implement the trial; it allows to assess the added value of the TMP upon the existing care and should thus meet with the least barriers in disseminating the trial results.

#### Text messages package

Eligible patients in the intervention condition will receive, via mobile phones, a package of 12 short (less than 120 Chinese characters) messages in 12 consecutive days (once a day). Detailed content of the messages is given in Table 1. Each of these messages was based on the main drivers of excessive antibiotics as identified from our previous studies [27] and has specific aims. For example, the message, to be sent out on day 1, aims to build trust and assure the patient not to worry about common RTI symptoms and most of which will start to mitigate within a few days and disappear within about 1 week. Similarly, the message to be sent on day 2 aims mainly to provide alternative ways for coping with RTI symptoms so as to divert his/her reliance on medications. While the message on day 3 tells the patient to postpone or avoid uptake of the antibiotics prescribed by his/her doctor.

**Table 1 Tab1:** Messages to be sent out to patients with symptomatic respiratory infections

**No.**	**Content of message**
Day 1	Dear [PatientName], many thanks for your trust and visit to our clinic for a [DiseaseDiagnosis]. What you were experiencing were mainly [PatientSymptom]. These are very common symptoms. They generally reach a peak within 1-3 days and then begin to relieve gradually. You needn’t see any doctor again unless you do not get better within [NormalDuration]. From [DoctorName] with [ClinicName].
Day 2	Dear [PatientName], the best way to deal with most respiratory tract problems such as [DiseaseDiagnosis] is to improve your own body immunity and what you need to do are only the following. First, eat more protein-rich and digestible foods, such as fish or egg soup. Second, eat more fresh vegetables, fruits, garlic and ginger. Third, have more rest and drink more warm water. From [DoctorName] with [ClinicName].
Day 3	Dear [PatientName], most of the respiratory tract health problems such as [DiseaseDiagnosis] do not need antibiotics, such as amoxicillin, cephalosporin, and others. The medications your doctor has prescribed for you are to be used only when there are clear indications. In other words, you need only take fever pills when you have high fever; you need only take antibiotics when your symptoms do not recover after [NormalDuration]. From [DoctorName] with [ClinicName].
Day 4	Dear [PatientName], [DiseaseDiagnosis] is easy to transmit to family members and friends. Please avoid contact with them, especially children and the elderly in the local community for 1-2 weeks. Please practice ventilating your living rooms, wearing masks when you go out or meet with people, avoiding eating out and going to crowded places. From [DoctorName] with [ClinicName].
Day 5	Dear [PatientName], most respiratory tract infections such as [DiseaseDiagnosis] are caused by virus. Generally, they are self-limiting without oral medicines or injections. Antibiotics do not work for viral infections, which can neither ease the severity of symptoms nor shorten the duration. Most importantly, antibiotics can cause antibiotic resistance and various other side effects. From [DoctorName] with [ClinicName].
Day 6	Dear [PatientName], taking antibiotics (such as amoxicillin and cephalosporin) will weaken your own body immunity, and will kill the good bacteria in your gut as well, or upset the balance of/in your stomach. The more antibiotics you take, the higher chance that you suffer from an antibiotic-resistant-infections. This infection is not only serious, but also difficult to treat and are easy to transmit to family members. From [DoctorName] with [ClinicName].
Day 7	Dear [PatientName], when you feel unwell with respiratory tract, you should not go to retail pharmacies to buy antibiotic. China National Medicine Administration Bureau has banned pharmacies to sell antibiotics to residents without a doctor's prescription. China National Health Commission advises not to have a drip or take antibiotics for coughs, cold, sore throat or earache. From [DoctorName] with [ClinicName].
Day 8	Dear [PatientName], are you feeling any better from your [DiseaseDiagnosis]? If yes, you seem to be recovering as expected; If not, you should better see your doctor again. As antibiotics do almost no good for respiratory tract infections but have many side effects, we recommend you clearly tell your doctor that you don't want antibiotics whenever you consult a doctor in the future; or, if you are prescribed with antibiotics, ask your doctor whether the antibiotics can be avoided. From [DoctorName] with [ClinicName].
Day 9	Dear [PatientName], your current illness suggests that every on including you can get respiratory tract infections. Therefore, you need to strengthen your personal protection in the future. This include: eat more fresh vegetables and fruits; exercise more; wash hands more frequently; avoid crowded places when many people around you are having respiratory symptoms and wear a mask when you go out. From [DoctorName] with [ClinicName].
Day 10	Dear [PatientName], a certain proportion of respiratory tract infections are influenza. Influenza is highly contagious and easy to increase the extra risk of common health conditions like chronic respiratory tract diseases and cardiovascular and cerebrovascular diseases. Therefore, the State encourages residents to get influenza vaccination, especially for the elderly over 60 years old, patients with chronic diseases, children aged 6 months to 5 years and caregivers for infants under 6 months. From [DoctorName] with [ClinicName].
Day 11	Dear [PatientName], after recovery from your current illness, if you have respiratory symptoms next time in the future, please do not hurry seeing a doctor but wait and watch its progression, do not go to retail medicine shop to buy antibiotics without a prescription, and do not take leftover antibiotics. Please practice rest at home, drink more water and eat more protein-rich and digestible food and more fresh vegetables. Most respiratory infections are self-limiting and the symptoms start to relief within a few days. From [DoctorName] with [ClinicName].
Day 12	Dear [PatientName], this is the last message we plan to send you. We hope you will do as what the messages have suggested and avoid antibiotics use whenever possible. Antibiotics have no effect on most respiratory infections - they cannot relief the severity of symptoms or shorten the disease duration. On the contrary, antibiotics are easy to cause drug resistance and various other side effects. Thank you for accepting and reading all the messages and all the best wishes for you. From [DoctorName] with [ClinicName].

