#### Eligibility criteria

The inclusion criteria for patients are presenting males or females to the site health centers who are (1) 18 years or older and able to give consent to participate in the patient survey and/or follow-up interviews; (2) diagnosed, by doctor, with common RTIs, including acute upper RTI, common cold, acute bronchitis/tracheitis, exacerbation of chronic obstructive pulmonary disease, and influenza-like illness; and (3) able to receive and comprehend messages via either self-reading or assistance from family members. Exclusion criteria are patients who (1) have previously sought treatment for the current illness from the participating health centers and (2) are pregnant individuals.

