#### Adverse event reporting

Given the nature of the intervention, we do not expect the occurrence of serious adverse events. Nonetheless, adverse events will be actively sought during each follow-up survey. All participants receive guidance to promptly inform the trial coordinator if they experience any events of concern. Additionally, the intervention is discontinued if a participant makes such a request, and if the investigator determines the participant’s inability to effectively utilize the intervention, or in the occurrence of a serious adverse event.

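### Days 1 and 3 tie return and use of prescribed antibiotics to a waiting period alone, and none of the 12 messages makes an exception for getting worse

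*Protocol article*

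**What the plan says.** Table 1, under Text messages package, gives the wording that patients receive. Day 1 says symptoms usually peak within 1 to 3 days and then ease, and that the patient need not "see any doctor again unless you do not get better within [NormalDuration". Day 3 opens with a general limit, "The medications your doctor has prescribed for you are to be used only when there are clear indications", and then restates it in other words. Fever pills are for high fever; for antibiotics, "you need only take antibiotics when your symptoms do not recover after [NormalDuration". The text above the table gives the aim: the Day 3 message "tells the patient to postpone or avoid uptake of the antibiotics prescribed by his/her doctor". On Day 8 the patient is asked about progress and, if not feeling better, advised to see the doctor again.

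Under Message tailoring, the program inserts values into a fixed template. The waiting period comes from a diagnosis-specific dictionary, and the one worked value is 14 days for a common cold. Under Message sending, the doctor may modify the template. Under Eligibility criteria, the diagnoses include "exacerbation of chronic obstructive pulmonary disease, and influenza-like illness". The only exclusions are treatment already sought for this illness at a participating center, and pregnancy.

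Under Adverse event reporting, the protocol says that, given the nature of the intervention, "we do not expect the occurrence of serious adverse events". Events are nonetheless actively sought at each follow-up survey, participants are told to "promptly inform the trial coordinator if they experience any events of concern", and the intervention stops on request, on a serious adverse event, or if the investigator judges that the participant cannot use it effectively.

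**The concern.** Advice to wait before returning, or before taking a prescribed medicine, normally carries a second condition: come back sooner if you get worse. Here that condition is absent from the two messages that give the waiting advice. A patient who deteriorates inside the waiting period finds nothing in the text that applies. Day 1's remark about a peak within 1 to 3 days may even make early worsening look expected. Each message is signed in the doctor's name, so Day 3 reads as the doctor qualifying the prescription.

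This affects only the message arm; usual-care patients get no text advising them to hold what was prescribed. It matters most for patients whose illness can progress, and COPD exacerbation is enrolled without a severity limit. The primary outcome counts days with any antibiotic, so it cannot by itself tell an unnecessary course avoided from a needed course delayed.

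**Working it through.** No figure in the plan has to be reproduced. The check is a reading of all 12 messages against one question: does the text say what to do if the current illness worsens?

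- Day 1: return is tied to no improvement within the waiting period. Worsening not mentioned.
- Day 2: diet, rest and warm water. Not mentioned.
- Day 3: antibiotics are tied to non-recovery after the waiting period. Not mentioned.
- Days 4 to 7: transmission, viral cause, harms of antibiotics, pharmacy purchases. Not mentioned.
- Day 8: see the doctor if not feeling better. A return prompt, but not one about worsening.
- Days 9 and 10: prevention and influenza vaccination. Not mentioned.
- Day 11: watch the progression of a future episode. It does not concern the current illness.
- Day 12: closing message. Not mentioned.

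Result: 0 of 12.

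Next, does Day 3's general limit supply the exception? Read alone, a clear indication could include worsening. But the message goes on to define the phrase: high fever for fever pills, elapsed time for antibiotics. A patient following the definition is left with time alone.

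Then, does tailoring supply it? Substitution changes the name, symptoms, diagnosis, doctor, clinic and duration. The conditions in the sentences stay the same for every diagnosis unless a doctor edits them, and no edit is required.

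Timing, as an illustration only, using the 14-day common-cold value counted from the consultation:

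- Message days before the Day 8 prompt: Days 1 to 7 = 7.
- From the Day 3 message to the end of the period: 14 − 3 = 11 days.
- From the Day 3 message to the Day 8 prompt: 8 − 3 = 5 days.
- From the Day 3 message to the first follow-up interview: 7 − 3 = 4 days.

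The gaps depend on the inserted value. If a diagnosis carried 7 days (an assumption, in line with the protocol's remark that most symptoms disappear within about a week), the wait from Day 3 would be 7 − 3 = 4 days, and Day 1's own condition would be reached before Day 8. The value for COPD exacerbation is not given.

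Patients planned to receive this text by default: 6 counties × 2 centers × 35 = 420.

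**The case against.** The case on the other side has substance. The messages come on top of usual care, so the consultation and any advice given there remain. The content of doctor training and of oral advice about worsening is not shown in a condensed article; it is unknown, not absent. Doctors may edit the template. Adverse events are actively sought, and there are stopping rules. Illness duration, severity and EQ-5D-5L are collected at days 7, 14 and 21, and re-visits and re-prescription at day 21, so harm from delay could show in the secondary outcomes. Some patients will have started their antibiotics before Day 3 arrives.

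All of this stands, and it limits the weight of the point. It does not answer it. These provisions lie outside the text the patient reads at home. The reporting advice directs the patient to the trial coordinator rather than to a clinician, active follow-up begins at day 7, and secondary outcomes detect a problem afterwards.

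Several stronger readings are tempting but unsupported:

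- That the messages forbid a visit. The Day 1 wording is permissive; the gap is a missing exception.
- That a number of COPD patients would go without needed antibiotics. The document gives neither the COPD share nor its waiting period, and any such count would also assume that every patient obeys Day 3.
- That the plan itself names COPD patients as a group at risk from waiting, on the strength of the Day 10 words "easy to increase the extra risk of common health conditions like chronic respiratory tract diseases". That message is about influenza and argues for vaccination.
- That every diagnosis faces an 11-day wait. That figure belongs to one common-cold example.
- That COPD patients need a different Day 3 instruction. That is a debatable change to the intervention, and it would clash with Days 5, 6, 8 and 12, which still discourage antibiotics.

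**Conclusion.** The point holds as a participant-safety gap in the message wording. Day 1 ties return, and Day 3 ties use of prescribed antibiotics, to a waiting period only; 0 of 12 messages provide for worsening; and the first return prompt independent of that period is on Day 8. The conclusion rests on the English wording in Table 1 being what the Chinese messages say, and on doctors not routinely adding the exception by hand. It needs no assumption about COPD share, adherence or effect size. No between-arm bias and no effect on antibiotic days is claimed. The wording should be corrected; the gap does not invalidate the trial.

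**What to change.** In Day 1, insert the words 'you get worse or' directly after 'unless', so that worsening stands beside lack of improvement as a reason to return. In Day 3, add one sentence: 'If you get worse, see your doctor.' Apply both to every diagnosis, as part of the default template, so that no hand edit is needed. The other ten messages, the dictionary of durations, eligibility and outcomes stay as they are.

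The cost is small. A few characters must fit under the 120-character cap in each of two messages. Recruitment opened on 1/12/2022, so the change goes through the route under Protocol amendments and deviations: sponsor permission, ethics approval, then a report to the registry. The downside is a mid-trial wording change that could slightly affect re-visits, a secondary outcome. Record the date of the new message version so that patients before and after it can be told apart.
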